## Abstract

**Background:**

It is encouraging to see a substantial increase in individuals surviving cancer. Even more so since most of them will have a positive effect on society by returning to work. However, many cancer survivors have unmet needs, especially when it comes to improving their quality of life (QoL). Only few survivors are able to meet all of the recommendations regarding well-being and there is a body of evidence that cancer survivors’ needs often remain neglected from health policy and national cancer control plans. This increases the impact of inequalities in cancer care and adds a dangerous component to it. The inequalities affect the individual survivor, their career, along with their relatives and society as a whole. The current study will evaluate the impact of the use of big data analytics and artificial intelligence on the self-efficacy of participants following intervention supported by digital tools. The secondary endpoints include evaluation of the impact of patient trajectories (from retrospective data) and patient gathered health data on prediction and improved intervention against possible secondary disease or negative outcomes (e.g. late toxicities, fatal events).

**Methods/design:**

The study is designed as a single-case experimental prospective study where each individual serves as its own control group with basal measurements obtained at the recruitment and subsequent measurements performed every 6 months during follow ups. The measurement will involve CASE-cancer, Patient Activation Measure and System Usability Scale. The study will involve 160 survivors (80 survivors of Breast Cancer and 80 survivors of Colorectal Cancer) from four countries, Belgium, Latvia, Slovenia, and Spain. The intervention will be implemented via a digital tool (mHealthApplication), collecting objective biomarkers (vital signs) and subjective biomarkers (PROs) with the support of a (embodied) conversational agent. Additionally, the Clinical Decision Support system (CDSS), including visualization of cohorts and trajectories will enable oncologists to personalize treatment for an efficient care plan and follow-up management.

**Discussion:**

We expect that cancer survivors will significantly increase their self-efficacy following the personalized intervention supported by the m-HealthApplication compared to control measurements at recruitment. We expect to observe improvement in healthy habits, disease self-management and self-perceived QoL.

*Trial registration* ISRCTN97617326. https://doi.org/10.1186/ISRCTN97617326. Original Registration Date: 26/03/2021.

## Background

Cancer is the second cause of mortality worldwide, with 18 million new cases in 2018 and 9.5 million deaths [1, 2]. A significant increase of new cases is expected in the next 20 to 40 years. In 2018, 3.91 million new cases of cancer (excluding non-melanoma skin cancer) were estimated in Europe [3], including approximately 1.6 million patients of working age [4, 5]. The most common cancer sites were breast (523,000 cases), followed by colorectum (500,000) [3]. The numbers of cancer surviors are increasing due to advances in cancer treatment and early detection are. In the EUROCARE study [6], the 1999–2007 European mean age-standardized 5-year relative survival for breast cancer (women only) was 81.8% (95% CI 81.6–82.0). For colorectal cancer, the European mean age-standardized 5-year survival was 57.0% (95% CI 56.8–57.3). More than half of the European cancer patients survive 5 years or longer after diagnosis leading to more cancer survivors who experience long-term or latent side effects as a result of cancer treatments [6].

It is very encouraging to see substantially more people surviving cancer, especially as many of them will have a positive effect on society. However, many cancer survivors have unmet needs, especially when it comes to improving the quality of life (QoL), in addition to lengthening of life span [7]. Study in [8] showed that approximately one in four survivors face moderate to severe physical or psychological issues after their cancer treatment. Some cancer survivors have levels of fatigue threefold greater than the general population [9], and many carry a life-long fear of cancer recurrence [10]. Cancer survivors from vulnerable populations or with a low-socioeconomic status are particularly at risk of having QoL lower as compared to the general population [11]. Returning to work had been observed as difficult for a significant number of survivors, A survey in [12] reports that over one-third of employers highlighted concerns about workplace discrimination against cancer survivors.

Fear of cancer recurrence, late toxicity limitations, comorbidities, nutritional disorders and high levels of psychological distress and depression, including the risk of suicide, are generally not appropriately assessed in the guidelines’ recommendations used in follow-up after treatment. However, scientific publications in recent years reflect the growing interest in evaluating and preventing these and other problems to improve the quality of life of cancer survivors.

In the last decades, evidence is emerging that lifestyle of cancer survivors positively influence cancer prognosis as for example, exercise [13], increased fruit and vegetable consumption, healthy body weight and body composition [14], smoking cessation [15], and cognitive behavioral therapy [9]. However, only few survivors can follow all of these recommendations [15]. There is significant research highlighting how the health policy and national cancer plans often neglected cancer survivors’ actual needs [16]. Furthermore, the increasing number of cancer survivors is likely to have a substantial economic impact on the health system.

The PERSIST European Project: "Patients-centered SurvivorShIp care plan after Cancer treatments based on Big Data and Artificial Intelligence technologies", was developed to improve health outcomes, QoL and promote stress reduction related to breast and colorectal cancer survivors, who have gone beyond curative cancer treatment. The choice of these two cancers was based on their relatively high incidence and survival rates, constituting a large number of survivors whose follow-up can be improved.

PERSIST consortium aims at developing an open and interoperable ecosystem to improve the care of cancer survivors. In the project, we expect to achieve increased self-efficacy and satisfaction with care. We also foresee a reduction in psychological distress due to better management of the consequences of cancer and treatment. Compared to usual care, PERSIST interventions are expected to (1) improve health and well-being and, where applicable, contribute to faster reintegration into the labor market, (2) to increase the effectiveness of cancer treatment and follow-up by supporting the decision-making with prediction models, trained on Big Data (3) contribute to more optimal treatment decisions that will reflect in positive (HR)QoL outcomes of survivors, and (4) improve information and evidence to increase the efficacy of management, intervention and prevention policies targeting timely treatment of side effects and, if possible, avoidance of secondary diseases and fatal events.

Several studies have shown how patients and survivors can benefit from digital tools and specifically, solutions that capture patient-reported outcomes (PROs) [17, 18] or solutions that capture patient gathered health data [19]. Nevertheless, the integration of digital tools in clinical settings still raises several different questions. The clinical study is specifically contemplated to assess the efficacy of patient interactions with a mobile device, the quality of data reported by patients using the mHeathApp, and data artificially classified using complex software sensors (i.e., mood estimation, recognition of symptoms of depression). A detailed understanding of different individual, intervention and design factors that have the potential to alter quality of collected data is needed [20, 21].

### Objectives and hypotheses

The objective is to determine if and how a mobile health system (mHealthApp), supported by data-driven Clinical Decision Support System (CDSS), both developed within the project PERSIST [22], will positively affect the behavior of survivors of breast cancer and colorectal cancer. The PERSIST intervention is expected to increase survivors’ self-efficacy and satisfaction with care as well as to reduce psychological stress for a better management of the consequences of cancer and its treatment. Intervention should result in an improved health outcomes and well-being. It should also re-integrate survivors into the labor market faster. By delivering prediction models from Big Health Data and a tool to support decision-making, PERSIST will enable clinicians to make optimal treatment decisions that have a positive impact on the survivor’s quality of life and health. The improved information and evidence will increase the effectiveness in cancer treatment and follow-up, i.e. effectiveness of management, intervention and prevention policies/strategies in order to respond quickly to the side effects and, if possible, avoid secondary diseases and fatal events, compared to regular routine. The long-term result is expected to reduce the socio-economic burden related to cancer survivors’ care.

The primary clinical objective is to assess the acceptability and usability of the mHealthApp and its impact on perceived self-efficacy and satisfaction with care from the perspective of the survivor. To evaluate the primary objective, two validated tools measuring self-efficacy can be utilized, Communication and Attitudinal Self-Efficacy scale for cancer (CASE-cancer) [23] and Strengths Self-Efficacy Scale (SSES) [24]. CASE-cancer was chosen since self-efficacy has been shown to be a protective effect for survivors who have higher perceived risk of recurrence [25–27]. Indivduals who are at higher risk with respect to health and well-being indicators may benefit more from the digital intervention.

The secondary clinical objectives include measuring the patient activation and acceptance of the mHealthApp and experience of its use among them. Patient activation represents the knowledge, skills, and confidence to manage one's health. In multiple chronic conditions, it has been shown to contribute to improved self‐management behaviors [28, 29]. More active patients are more likely to believe their treatment plans reflect their values, more likely to face side effects, and more likely to initiate a healthier diet after diagnosis than less active patients [30]. Less active patients are less likely to understand their diagnosis, follow treatment regimens, and be satisfied with their care. System Usability Scale (SUS) [31], and User Experience Questionnaire (UEQ) [32] will be used to assess acceptance, user experience and possible issues regarding the use of mHealth App. Factors with significant impact on behavioral intention and motivation of use of mHealth Apps are perceived usefulness and ease of use, perceived risk and trust, the subjective norm and attitude [33]. Perceived ease of use is especially significant factor for middle-aged and older survivors.

Finally, the secondary clinical objectives also include the evaluation of the effectiveness of health monitoring and patient gathered health data (PGHD). PGHD includes self-reported health and treatment histories, patient-reported outcomes (PROs), and biometric data [34]. There is a growing interest in PGHD in oncology. Namely, patient reported symptomatology tends to provide a significantly richer information source then Clinicians’ ratings of adverse events. Moreover, there is increasing evidence that integrating PGHD into clinical care can improve outcomes over standard care [35]. Despite the abundance of opportunities, the uptake of digitals tools is surprisingly slow. The two major concerns are the interpretation and quality of data and the concern that reliance on PGHD from wearable devices could exacerbate health disparities, especially in elderly and individuals with less-favorable socioeconomic situations [35–40]. Especially in PROs, the quality of self-reported data depends upon respondents’ ability and willingness to provide accurate and valid responses. Inattentive or careless is defined as an action in which respondents provide answers for the sake of the survey (i.e., a form of survey “satisficing”.) [40]. Thus the respondent does not fully read and/or interpret the question and fails to generate a meaningful response. To measure possible inattentive and carless in responding, we will deploy the Directed Questions Scale—DQS [41].

#### Hypothesis

Performing a comparison between the beginning and the end of the intervention, participants will significantly increase their self-efficacy following the personalized intervention supported by the mHealthApp.

#### Primary and secondary endpoints

The primary endpoint is defined as: *increased perceived self-efficacy in participants (80 colorectal, 80 breast cancer survivors from the 4 pilot hospitals) following the mHealthApp supported intervention as measured using CASE-cancer scale for cancer as the validated standardized measure.*

The secondary endpoints include:observing modifications in patient activation levels measured using the PAM,observing modification in User acceptance depending on the level of support measured via SUS and UEQ,description of negative outcomes over time: hospitalization, exacerbations, treatment adherence, depression, recurrence, drug escalation,impact of variable modes of delivery (e.g., conversational agent) on quality of answers measure with DQS,the impact of patient trajectories (extracted from retrospective data) and PGHD on prediction of possible secondary disease or negative outcome,the impact of patient trajectories (extracted from retrospective data) and PGDH on improved intervention against the appearance of secondary diseases, worsening late toxicities or development of fatal events (sudden death, suicide).

## Methods/design

### Study design

A single-case experimental prospective study was designed in alignment with single-case experimental design (SCED) methodology [42]. Within SCED, each individual is his/her own control group based on the first measurement prior to the intervention. The SCED was selected since single-case designs can capitalize on the ability of technology to easily, unobtrusively, and repeatedly assess health-related behavior [43]. The study design is highlighted in Fig. 1. It is based on the Changing Criterion design in which the intervention and delivery of intervention are modified through personalization of (a) goals/tasks and (b) with spoken language interfaces and embodied conversational agents to complement the regular baseline delivery mode via the digital interfaces of the mHealthApp. The study will take place between 1st of May 2021 and 31st of December 2022, with the recruitment period between 1st of April 2021 and 15th May 2021. Data collection is first carried out prior to intervention, during recruitment round (T1). Each recruited individual will sign a letter of consent and fill in CASE-cancer and PAM questionnaires. The SUS questionnaire responses, along with CASE-Cancer and PAM will be collected following a baseline phase (T2) which will last for 6 months. During this phase a ‘generic’ intervention will include a recording of the diary (at least 3 times a week), report regarding their emotional state (at least once a day) and answering a specific PRO for reporting Health Related QoL and symptoms (a different PRO each day). In total, we expect 10–15 min of interaction every day. T2 will conclude with the first follow-up with clinician, during which data regarding primary (CASE-Cancer, PAM, SUS/EUQ) and secondary endpoints will be collected. The personalized intervention phase (T3) will include execution of tasks on mHealth App personalized for the survivor. The data collection tools will remain the same, however the responsible oncologist will define which of the tools the patient must implement (e.g., which PROs) and in what frequency, depending on the risk assessment implemented by the clinical staff. During intervention, specific tools may change depending on the risks detected for the specific patient. T3 concludes with a follow-up during which data regarding primary/secondary endpoints (CASE-Cancer, PAM, SUS/UEQ). A first comparison between generic intervention and personalized intervention will be made. The AI supported clinical intervention (T4) will introduce embodied conversational agent EVA [44] and AI-drive risk assessment engine to deliver fully personalized intervention and to demonstrate that the data-driven models developed within PERSIST can improve quality of life of cancer survivors by acquiring, managing, sharing, and processing big data to create overall actionable insights at the point of care.

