#### Patient information and informed consent

Clinical partners will develop an informed consent document translated in their local language and will apply for their local or national bioethics committee approval. GDPR regulation will be strictly followed to protect personal data of participants. Each center will be responsible to obtain a signed informed consent from the patient before inclusion in the study. The participants will be recruited by 4 hospitals involved in the study from different EU countries (Belgium, Latvia, Slovenia and Spain). Every clinical partner will involve 40 survivors, 20 patients from C18/C19 (Colorectal cancer) and 20 patients from C50 (breast cancer). In total 160 patients will be recruited to participate in envisioned two-phases clinical study. The recruitment stage will begin in April, 2021. The study will involve breast and colorectal cancer patients who have survived beyond curative cancer treatment. We will consider a survivor patient all breast and colorectal cancer patients who survive without recurrence beyond 3–24 months after the end of treatment (surgery ± radiation therapy ± chemotherapy), they have received. For colorectal cancer survivors' group, two subgroups will be included (chemotherapy and non-chemotherapy). None of the groups will be lower than 33% in ratio to the other. For breast cancer survivorspatients that have had surgery and patients that have had chemotherapy.

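### Fixed-order phases after a single pre-app measurement can show change over time, but cannot attribute it to the app, personalisation or the conversational agent, or set it against usual care

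*Protocol article*

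**What the plan says.** All references are to the protocol article.

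- **Control.** Under Study design, "each individual is his/her own control group based on the first measurement prior to the intervention".
- **Timing.** "Data collection is first carried out prior to intervention, during recruitment round (T1"); CASE-cancer and the Patient Activation Measure (PAM) are taken then. They are repeated "following a baseline phase (T2) which will last for 6 months", and again at the end of T3 and T4. Table 1 shows the same four time points. The T2 phase is not untreated: it contains a generic app programme of diary recordings, daily mood reports and daily questionnaires.
- **Order.** Everyone moves from the generic app (T2) to the oncologist-personalised app (T3) to the AI-supported phase (T4). That last phase "will introduce embodied conversational agent EVA [44] and AI-drive risk assessment engine".
- **Entry.** Participants are "patients who survive without recurrence beyond 3–24 months after the end of treatment".
- **Formal hypothesis.** Self-efficacy is compared between the start and the end of the intervention (Hypothesis).
- **Further claims.** At the end of T3, "A first comparison between generic intervention and personalized intervention will be made". T4 is meant to demonstrate that the project's data-driven models can improve quality of life. A secondary endpoint is "impact of variable modes of delivery (e.g., conversational agent) on quality of answers measure with DQS". The Background states: "Compared to usual care, PERSIST interventions are expected to (1) improve health and well-being and" goes on to faster return to work. The Discussion repeats the usual-care comparison for health, well-being and labour-market integration.
- **Analysis.** The Statistical analysis section compares pre, post and follow-up values. It also compares negative outcomes and patient trajectories with retrospective data.

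**The concern.** A single-case experimental design supports causal statements when something separates the phase from elapsed time: a repeated series before the intervention, a withdrawal phase, or staggered or randomised phase starts. For CASE-cancer the article describes none of these. Each contrast is therefore the phase effect plus whatever else changes over the same months: recovery after treatment, repeated exposure to the questionnaire, familiarity with the app, and calendar events. Entry 3 to 24 months after treatment makes recovery plausible.

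A significant T1–T4 rise could then be reported as an effect of the app even if survivors improve without it. A T2–T3 difference could be reported as the benefit of personalisation, and a better Directed Questions Scale (DQS) result in T4 as the benefit of the agent.

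**Working it through.** **1. What each contrast contains**

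| Claim | Contrast available | What else differs |
|---|---|---|
| App raises self-efficacy | T4 v T1 | about 18 months (3 × 6) of elapsed time |
| Personalised v generic delivery | T3 v T2 | 6 further months and prior app exposure |
| Agent improves answer quality (DQS) | T4 v T2/T3 | elapsed time, prior exposure, and the AI risk engine that starts with the agent |
| Models improve quality of life | T4 v earlier phases | elapsed time, prior exposure, and the agent that starts with the engine |
| Better than usual care (well-being, return to work) | none | no usual-care data on these outcomes |

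The Data collection section confirms the third row: answers are collected manually in T2 and T3 and with agent support in T4, so mode follows phase.

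**2. The plan's own sample-size figure**

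Inputs from Sample size calculation: two dependent means, two-sided 5%, power 90%, d = 0.25, n = 160. The noncentral t calculation gives n = 171 for 90% power, and 88.2% power at n = 160. The stated 160 is therefore not reproduced exactly. That is a separate matter and does not affect this point.

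**3. How often drift alone would be significant**

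Assume no app effect and a mean drift of δ, in SD of the change. The paired t statistic has 159 degrees of freedom, critical value 1.975 and noncentrality δ√160 = 12.649 δ.

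| Assumed δ | 12.649 δ | P(p < 0.05) |
|---|---|---|
| 0 | 0 | 5.0% |
| 0.05 | 0.632 | 9.6% |
| 0.10 | 1.265 | 24.2% |
| 0.15 | 1.897 | 47.1% |
| 0.20 | 2.530 | 71.0% |
| 0.25 | 3.162 | 88.2% |

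A drift equal to the planned effect of 0.25 is declared significant as often as a true effect of that size. Spread over 18 months it is 0.25/18 = 0.014 SD per month. The same table applies to one phase contrast: a drift of 0.10 between T2 and T3 gives 24%.

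The direction could be the opposite. A true effect of 0.25 with a drift of −0.10 leaves a net 0.15, and power falls from 88% to 47%.

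**4. Could adjusting for time since treatment rescue the attribution?**

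Within a person, elapsed time and phase are collinear, so the recovery slope can come only from differences between people at entry. Take 160 people with entry spread evenly over 3–24 months, linear recovery, and within-person correlation ρ of 0.3 to 0.7. Generalised least squares then gives a standard error for the T4 effect of 0.186 to 0.214 SD of the score, against 0.094 to 0.061 unadjusted (√(2(1−ρ)/160)). An effect of 0.25 SD of the change is 0.25√(2(1−ρ)) = 0.296 to 0.194 SD of the score. Power is about 36% to 15%. The model also assumes that early and late entrants are comparable. It is too weak to help.

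**The case against.** The strongest reply is that the formal question is already a before-after one. The hypothesis compares start with end, the abstract takes the recruitment measurement as the control, and the Statistical analysis section calls the study mainly a pilot of acceptability and usability. This stands. A reader might infer that the primary hypothesis is unanswerable or its test invalid, but the documents do not support that: the change can be estimated, and only its attribution fails.

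A reader might also infer that the trial promises to test self-efficacy against usual care. It does not. The usual-care phrases are expectations in the Background and Discussion, attached to health, well-being, labour-market integration and follow-up. No listed endpoint or test uses usual care.

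Nor is there no comparator at all. Retrospective data are used, but only for negative outcomes and trajectories. They do not cover CASE-cancer, PAM, quality of life or return to work.

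Two passages are ambiguous. Study design says the agent complements the regular digital interface, so the screen mode may remain in T4; Fig. 1 is not visible. Even so, no allocation between modes within T4 is described, so those who choose each mode may differ. The Outcomes section labels the four batteries pre-screening, T1, T2 and T3, which could suggest a second early measurement. Study design and Table 1 show only one before the app.

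Frequent in-app data offer more time points for symptoms and quality of life. But there is no pre-app series, and the questionnaires and their frequency change at T3.

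**Conclusion.** The point holds as a limit on conclusions. The T1–T4 change in CASE-cancer can be estimated. The following are not identified by the design as described: attribution to the app, personalised versus generic delivery, the agent's effect on DQS, the demonstration that the models improve quality of life, and superiority to usual care on well-being and labour-market integration.

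The size is illustrative. The 24% to 88% range assumes an upward drift of 0.10 to 0.25 SD of the change, complete data on 160 patients and no app effect. The documents give neither the size nor the direction of any drift, so these figures should not be read as the trial's false-positive rate.

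This should be fixed. It is not a fatal flaw, because the formal hypothesis is answerable and the necessary change is to what is claimed.

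**What to change.** 1. Describe the T1–T4 CASE-cancer result as uncontrolled within-person change in app users.
2. Report T2–T3 and T3–T4 differences as changes over time, not as effects of personalisation, the agent or the AI risk engine.
3. Remove the usual-care statements and the claim that T4 will demonstrate improved quality of life, or mark them as not testable in this study. State that the retrospective comparison covers negative outcomes and trajectories only.

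These three changes cost wording only.

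Optional, for the DQS endpoint: randomly assign a share of T4 questionnaire sessions to the existing screen mode, and compare modes within patient within T4. This separates answer mode from both elapsed time and the AI risk engine. It needs a change to the app and gives slightly less exposure to the agent in T4.

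A model adjusting for time since treatment is not recommended as a remedy, for the reasons shown in the working.

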#### Study setting

The study will involve 160 survivors (80 survivors of Breast Cancer and 80 survivors of Colorectal Cancer) from four countries, Belgium, Latvia, Slovenia, and Spain. Each of the sites will recruit 40 cancer survivors according to the inclusion/exclusion criteria. Study will involve the use of digital intervention during every-day activities outside the clinical environment (i.e., at the subjects’ homes). The data collected will be evaluated during regular 6 month follow ups.

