#### Sample size calculation

To estimate the sample size to difference between two dependent means we have based on the assumptions of a two-sided confidence level of 95%, a statistical power of 90% and effect size Cohen’s *d* of 0.25. The previous assumptions indicate that 160 patients may detect differences between pre and post variables of healthy habits. A G*Power 3.1 software was used to make this sample size estimation.

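### Six-week spring recruitment and fixed-order 6-month phases tie phase to season for everyone, so generic-versus-personalised and first-versus-last comparisons of healthy habits and mood are confounded with season

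*Protocol article*

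**What the plan says.** The Study design section of the protocol article sets the calendar. Enrolment is confined to a single spring, "with the recruitment period between 1st of April 2021 and 15th May 2021", and the study closes at the end of 2022. Generic use of the app fills a "baseline phase (T2) which will last for 6 months". The lengths of the personalised and AI-supported phases are not given directly. They follow from the visit schedule: the Abstract has "subsequent measurements performed every 6 months during follow ups" and Study setting has "The data collected will be evaluated during regular 6 month follow ups".

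The phase order is the same for all, each participant is their own control, and all four sites are in Europe. The Hypothesis section compares the start of the intervention with its end. Study design adds, after the T3 visit: "A first comparison between generic intervention and personalized intervention will be made".

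Healthy habits matter to the trial although they are not listed endpoints. The Abstract states: "We expect to observe improvement in healthy habits, disease self-management and self-perceived QoL". Study itinerary says that habits and quality of life will be analysed, and the Sample size calculation concludes that "160 patients may detect differences between pre and post variables of healthy habits". Depression appears among the negative outcomes in the secondary endpoints. The Statistical analysis section plans pre, post and follow-up tests and sub-analyses by cancer type, sex and other variables of interest. It does not mention calendar time.

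**The concern.** In a before-after design with no concurrent control, no staggered start and one phase order, anything that changes with the calendar changes with the phase. Season is a specific and foreseeable case. Steps, physical activity, diet and mood plausibly differ between summer and winter, and here every participant meets the same season in the same phase. Stratifying by cancer type or sex cannot help, because season does not vary between participants within a phase.

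A personalised phase that works could look ineffective on activity or mood because it runs through winter, and the AI phase could look effective because summer returns. The reverse errors are possible too. Unlike recovery or a general time trend, this bias can be removed largely by choosing which periods to compare.

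**Working it through.** **The plan's own figure.** The sample size uses a paired comparison, two-sided 5%, 90% power and d = 0.25, and states 160. The exact paired t-test (noncentral t) needs 171; 160 gives 88.2% power. That gap is a separate matter and does not bear on this point. I use n = 160 and d = 0.25 below as the plan's reference values.

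**Calendar.** Visit date = entry date + 6, 12 and 18 months.

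| Entry (T1) | T2 | T3 | T4 |
|---|---|---|---|
| 1 Apr 2021 | 1 Oct 2021 | 1 Apr 2022 | 1 Oct 2022 |
| 15 May 2021 | 15 Nov 2021 | 15 May 2022 | 15 Nov 2022 |

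All visits fall before the stated end of the study. Days per phase, the same at both ends of the window:

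| Phase | June–August days | December–February days |
|---|---|---|
| Generic | 92 | 0 |
| Personalised | 0 | 90 |
| AI-supported | 92 | 0 |

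Generic versus personalised is therefore a whole summer against a whole winter, and T1 versus T4 is April–May against October–November. T1 versus T3, T2 versus T4 and generic versus AI phase are each matched on season, one year apart.

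**Sensitivity to the recruitment window.** Participants and recruitment gives a 3-month period with 1 month of active enrolment. If entry ran as late as 30 June 2021, that participant would have 63 summer and 29 winter days in the generic phase, 29 and 61 in the personalised phase, and 63 and 29 in the AI phase. The overlap is blurred, not removed.

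**Size.** The documents give no seasonal effect, so the shift s, in SDs of the paired difference, is an assumption. With no intervention effect, the probability of significance is P(|T| > t) with T noncentral t, 159 degrees of freedom, noncentrality s × √160 = 12.65 s, and t the two-sided 5% critical value.

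| Assumed shift s | Noncentrality | Significant with no true effect | Power if the shift opposes a true d = 0.25 |
|---|---|---|---|
| 0.05 | 0.63 | 9.6% | 71% |
| 0.10 | 1.26 | 24% | 47% |
| 0.15 | 1.90 | 47% | 24% |
| 0.25 | 3.16 | 88% | 5% |

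With no seasonal shift the power is 88%.

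**Example in steps, all inputs assumed.** With 7000 steps a day and a seasonal difference of 5–10%, the shift is 350–700 steps. For an SD of paired change of 2500, s = 350/2500 = 0.14 to 700/2500 = 0.28, and the probability of significance is 42–94%. For an SD of 3500, s = 0.10 to 0.20 and it is 24–71%. For an SD of 5000, s = 0.07 to 0.14 and it is 14–42%.

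**The case against.** - **The generic-versus-personalised sentence names no habit outcome.** It follows a list of CASE-cancer, PAM, SUS and UEQ, and the Statistical analysis section names CASE-cancer and SUS/UEQ. Steps and GPAQ activity are not endpoints. This stands. A reader might infer that a summer-versus-winter test of steps is planned; the article does not say so. The point rests on the intention to analyse habits and on the sample size being tied to them.
- **The primary comparison.** A reader might infer that the CASE-cancer result is biased by season. Nothing in the documents indicates that self-efficacy is seasonal.
- **The T1 habit value.** A reader might conclude that no pre-app value exists. That is too strong. The article places CASE-cancer, PAM, clinical, demographic and social data and quality of life at T1, and Table 1 issues the smartwatch at recruitment. It locates no activity or nutrition measure at T1, but the full protocol may. For any outcome not measured at T1 there is also no T1-versus-T4 contrast to be confounded. That part applies only to outcomes measured at both visits.
- **The size is assumed and fragile.** It depends heavily on the SD, it counts significance in either direction, and one shift need not fit both contrasts. So 42–94% is not a rate of false claims of benefit.
- **Season is one case of the weakness of any uncontrolled before-after study,** in what the article calls mainly a pilot. True, but season is a part of that weakness that the existing design can address.

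**Conclusion.** The point holds as a low-cost improvement for healthy habits and mood. On the protocol's dates, phase and season coincide for every participant, so a generic-versus-personalised difference on these outcomes, or a T1-versus-T4 difference where both values exist, cannot be attributed to the intervention.

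The conclusion assumes that the later phases last 6 months, as the visit schedule implies, and that these outcomes vary with season, which is plausible but not quantified in the documents. The direction is unknown. If the shift is as small as 0.10 SD, a test with no true effect would reach significance in about 24% of trials instead of 5%; at 0.14 to 0.28 SD the figure is 42 to 94%. It does not follow that the primary analysis is invalid, or that the generic-versus-personalised comparison must be dropped.

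**What to change.** For activity, nutrition and mood, pre-specify the season-matched contrasts and report them beside the planned ones:

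- Device data: generic phase versus AI phase, within May–October 2021 and May–October 2022, pairing for each participant the same calendar dates in the two phases.
- Questionnaires taken at the visits: T1 versus T3 and T2 versus T4, shown next to T1 versus T4.
- State that generic versus personalised on these outcomes is descriptive and will not be read as an intervention effect.
- If the full protocol does not already do so, collect the GPAQ and the nutrition questionnaire at T1 before app use, so that the sample-size variable has a pre-intervention value.

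The cost is a few lines of analysis text and two short questionnaires at an existing visit.

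Season matching has limits. It does not remove recovery (participants enter 3–24 months after treatment) or other secular trend. T1 versus T3 leaves out the AI phase, and T2 versus T4 has no pre-intervention value. The personalised phase has no matched period for device data. Because the oncologist chooses the patient-reported tools and their frequency from the personalised phase on, some matched comparisons may have less common data.
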